### Outcome Measures

Baseline assessments will be carried out at Hemophilia Association centers. Measurements will be performed by a physiotherapist who is unaware of patient group assignments.

After the treatment period and 3 months after completion, the patients included in both groups (experimental and control) will be re-evaluated by the same rater under the same conditions as their initial evaluation.

Dependent variables (range of motion, joint pain, functionality, joint state, muscle strength, muscle flexibility, and record of activity) will be measured at each study assessment (baseline, posttreatment, and follow-up). A 10-point visual analog scale will be used to evaluate patient perception of joint pain, ranging from 0 (no pain) to 10 (maximum perceived pain). An algometer (FPN100; Wagner Instruments) will be used for the assessment of pressure-induced pain (the amount of pressure at which the person perceives pain), both at the joint and at other body sites [28]. Pressure will be applied gradually at the site, increasing at rate of 50 kPa/s until the patient reports that the sensation is painful [29]. In patients with ankle arthropathy, bilateral measurements will be taken anterior to the lateral malleolus (ankle) [30] and at two other sites—the spinous process of the L5 vertebra and on the extensor carpi radialis longus muscle of the forearm (5 cm distal to the lateral epicondyle of the humerus) [28]. Using a portable instrument [31] for assessing physical activity, patient physical activity level (average number of steps per day, average distance per day, average amount of active time, and energy consumption) will be recorded. The Hemophilia Joint Health Score [32] will be used to evaluate the joint condition of knees, ankles, and elbows. It includes 8 items (inflammation and its duration, pain, atrophy and muscle strength, crepitus, and reduced flexion and extension) ranging from 0 to 20 points per joint (the higher the score, the greater the joint deterioration).

The 6-minute walking test [33] measures the distance walked over a period of 6 minutes as an assessment of submaximal capacity to perform exercise. This instrument was developed for use in patients with respiratory disease and heart failure, but has been used in children and adults with a variety of chronic conditions, including hemophilia [34-36]. The test is performed on a 30 to 50-meter track, and the use of walking aids or orthopedic devices is permitted. Ankle range of motion will be measured by a digital goniometer using a protocol designed by Thornton et al [37]; the assessment can be performed with the patient standing. The axis of the goniometer will be placed alongside the lateral malleolus of the ankle. The fixed arm will be placed parallel to the fibula while the mobile arm is aligned to be parallel with the fifth metatarsal bone. This measuring instrument allows more accurate measurements than those obtained with a plastic goniometer. The patient will be asked to perform 3 repetitions of each movement. The mean of the 3 measurements will be used [28]. The maximum isometric strength of the plantar flexor muscles of the ankle will be evaluated on both limbs with a manual dynamometer. The patient will be placed in a supine position with 90º ankle dorsiflexion. The dynamometer will be located proximal to the metatarsophalangeal joints on the plantar side) and will be held by the evaluator [38]. The patient will be asked to perform 3 maximal effort isometric contractions (each for 5 seconds with a 30-second break in between) against the dynamometer and the mean of the 3 measurements will be used [28]. The fingertip-to-floor test [39] assesses the degree of flexibility of the posterior muscles of the lower limbs. The distance between the fingertips and the floor is calculated at maximum hip flexion with knees extended.

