**Methods:**

Patients with ankle arthropathy (N=70) will be recruited, enrolled, and assigned to one of two groups—experimental or control—in a 1:1 allocation ratio. Patients will be recruited from 5 centers in different regions of Spain. Patient data will be collected at baseline, posttreatment, and follow-up. The primary outcome will be frequency of ankle joint bleeding (self-reported). The secondary outcomes will be ankle range of motion (measured with a digital goniometer); joint pain (measured with a visual analog scale and an algometer); joint status (measured using the Hemophilia Joint Health Score); muscle strength (measured with a dynamometer); functionality of lower limbs (measured using the 6-minute walking test); activity (self-reported); and muscle flexibility (measured using the fingertip-to-floor test). The treatment program includes 11 exercises that must be administered bilaterally. A mobile app will be developed where each patient will be able to observe the exercises to be carried out. Each session will last 15 minutes with 5 physiotherapy sessions per week for a period of 3 months. It is expected that patients with hemophilia who receive the foam roller intervention will show improvement in mobility, pain, and status of the ankle joint; muscle strength; and function in the lower extremities.

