The objective of this paper is to describe our approach to the design and implementation of a protocol for self-myofascial release using a foam roller for patients with hemophilic ankle arthropathy with the aim of reducing the frequency of joint bleeding; improving range of motion; reducing joint pain; and restoring functionality, structural integrity, muscle flexibility, and muscle strength.

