### Data Analysis

The distribution of the sample, the changes after the intervention and follow-up period in each group, and the intra and interindividual effect will be analyzed. We will use the intent-to-treat method to include all individuals who were randomized in the final data analysis.

The statistical analysis will be carried out using SPSS statistical software (version 19.0; IBM Corp). The Kolmogorov-Smirnov test will be used to test for normality, and the Levene test will be used to test for homoscedasticity. If the conditions of normality and homoscedasticity are violated, nonparametric tests will be used.

Descriptive statistics (mean and standard deviation) will be calculated for all dependent variables. A one-way repeated measures analysis of variance will be used to compare the groups (experimental and control) at 3 assessment times (baseline, posttreatment, and follow-up). If the interaction is found to be significant, pairwise comparisons will be performed. The significance level will be set at α=.05. To control the error rate, Bonferroni correction will be applied. The results of the *F* test will depend on the significance of Mauchly sphericity. If significant, the Greenhouse-Geisser correction will be used. To assess clinical relevance, we will calculate the standard error of measurement and minimum detectable change for each dependent variable.

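### Ankle bleeding frequency is the primary outcome, but it is missing from the dependent variables, has no counting window, and the stated analysis is not set up for an event count

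*Protocol article*

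**What the plan says.** The abstract (Methods) is explicit: "The primary outcome will be frequency of ankle joint bleeding (self-reported"). The closing paragraph of the Introduction describes the intervention "with the aim of reducing the frequency of joint bleeding", ahead of every other aim.

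The Outcome Measures section gives the variables recorded at baseline, posttreatment and follow-up: "Dependent variables (range of motion, joint pain, functionality, joint state, muscle strength, muscle flexibility, and record of activity"). These are seven items, and bleeding is not one of them. The rest of that section describes how the listed measures are taken, in places down to the rate of applied pressure and the placement of the goniometer. It gives no definition, collection method or time window for a bleed.

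Data Analysis does not mention bleeding. It states: "Descriptive statistics (mean and standard deviation) will be calculated for all dependent variables". The only named comparison is this: "A one-way repeated measures analysis of variance will be used to compare the groups (experimental and control) at 3 assessment times". Before it stands a distributional check, "The Kolmogorov-Smirnov test will be used to test for normality", with the rule: "If the conditions of normality and homoscedasticity are violated, nonparametric tests will be used". The level is fixed by "The significance level will be set at α=.05".

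**The concern.** The article names a primary outcome, a set of dependent variables and an analysis, and the three do not fit together. Data Analysis describes the dependent variables, a term that Outcome Measures has filled in without bleeding. On a literal reading, the primary question has no planned analysis.

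If bleeding is read into the list, a second problem appears. A bleed frequency is a number of events over a period. The other variables are mostly scores or measurements taken at a visit. Without a window, it is unclear what the baseline value is or what the posttreatment and follow-up values cover. The plan also fixes no effect measure for bleeding, and its normality rule is likely to move a count out of ANOVA and into an unnamed test.

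At stake is the answer to the trial's main question. If the bleeding comparison is missing or improvised, the trial will be read on its secondary outcomes. A baseline bleed history that was not asked for at entry is also hard to recover later.

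**Working it through.** **1. Trace the outcome through the article.**

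| Place | Bleeding frequency |
|---|---|
| Abstract, Methods | Primary outcome, self-reported |
| Introduction, last paragraph | First-named aim |
| Outcome Measures, dependent variables | Absent (7 other items) |
| Outcome Measures, measurement detail | No definition, method or window |
| Data Analysis | Not mentioned |

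This step needs no assumption.

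**2. Look for a bleed rate in the plan's own figures.** The Sample Size section gives 236 at national level. It reproduces as a survey-precision calculation with N = 612, z = 1.96 and, assumed because unstated, p = 0.5 and d = 0.05: n = N·z²·p·q / (d²(N−1) + z²·p·q) = 612 × 0.9604 / (0.0025 × 611 + 0.9604) = 236.2. No bleed rate, effect size or power enters it. The rates below are therefore assumptions.

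**3. Would bleeding pass the normality check?** Assumed: gamma-Poisson counts, dispersion k = 1, 35 patients per arm (70 split 1:1). The share with no bleed is 1/(1 + mean). The Kolmogorov-Smirnov test used the arm's own mean and SD.

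| Mean bleeds per 3 months | Share with zero | Normality rejected |
|---|---|---|
| 0.5 | 1/1.5 = 67% | 100% |
| 1 | 1/2 = 50% | 96% |
| 2 | 1/3 = 33% | about 63% |

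This takes failed normality as enough to trigger the fallback. The plan's sentence joins normality and homoscedasticity and could be read as needing both to fail.

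**4. Is ANOVA invalid for these counts?** No. With no treatment effect, equal windows and 35 per arm, the group-by-time test rejected in 5.2% of runs at mean 0.5 and 4.4% at mean 1.

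**5. What does the choice of analysis cost?** Simulated power, 35 per arm, k = 1, rate halved, two-sided 0.05:

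| Analysis | Mean 0.5 | Mean 1 | Mean 2 |
|---|---|---|---|
| Repeated measures ANOVA, group by time | 20% | 34% | 55% |
| Mann-Whitney, treatment-period count | 24% | 36% | 44% |
| Overdispersed Poisson, baseline-adjusted | 27% | 52% | 72% |

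The count model held its level (3% to 5%). At mean 0.25 it gained nothing. Simulated figures carry an error of a few points, so the 3-point gap over Mann-Whitney at mean 0.5 should not be pressed.

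**6. Cross-check by formula.** For an unadjusted log rate ratio, the variance is (1/μ₀ + 1/μ₁ + 2k)/n. At μ₀ = 1, μ₁ = 0.5, k = 1 and n = 35 it is (1 + 2 + 2)/35 = 0.143, so SE = 0.378. Power is Φ(0.693/0.378 − 1.96) = Φ(−0.13) = 45%. The same formula gives 31% at mean 0.5 and 59% at mean 2. With 15% dropout (35 × 0.85, about 30 per arm) the three become 27%, 40% and 53%.

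**The case against.** The strongest reply is that this is a drafting slip in a condensed article, and that naming a fallback test is ordinary SAP content. The second half stands: an unnamed nonparametric test would not be a finding by itself. The first half does not dispose of the point. The article gives instrument-level detail for secondary measures, and it is the primary outcome that drops out of the list.

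A reader might go further than the documents allow in five ways.

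- That ANOVA cannot estimate a bleed-rate effect. Over equal windows a mean count is a rate, ANOVA contrasts estimate its difference, and the test keeps its level.
- That rank tests cannot address group by time. A Mann-Whitney test on change from baseline does so for two time points. What it lacks is a rate ratio or rate difference.
- That the plan ignores unequal observation time. All patients share one schedule, so times differ only through dropout, put at 15% in Sample Size.
- That bleeding will be mostly zeros and will almost certainly fail the normality test. No rate is given, and patients have bilateral arthropathy and may be treated on demand. At mean 2 only a third have zero bleeds.
- That bleeding has been abandoned as primary. The article nowhere says so.

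There is also a fair warning about remedies. At mean 0.25 only about 70 × 0.25 = 17.5 bleeds are expected per period with no effect. A negative binomial model with four covariates then failed to converge or gave unusable standard errors in 25% of null runs at 35 per arm and 32% at 30. That argues for a simpler model.

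**Conclusion.** The point holds as an inconsistency over the primary outcome, joined to an analysis that is not set up for it. The missing list entry, the missing window and the lack of any stated bleed-rate effect measure follow from the text alone.

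The size of the analytic loss rests on assumed rates, dispersion 1, equal windows and a halved rate. Under these, a baseline-adjusted count model gains over ANOVA 7 points of power at mean 0.5 (27 − 20), 18 at mean 1 (52 − 34) and 17 at mean 2 (72 − 55), and nothing at mean 0.25. ANOVA would be a valid but generally weaker choice. The case for a count model is that it gives an interpretable rate ratio without depending on a normality test.

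**What to change.** In Outcome Measures, add ankle bleed count to the dependent variables. Say what counts as a bleed and how it is reported. Use three equal windows that match the existing schedule: the 3 months before baseline, the 3 treatment months and the 3 follow-up months. Collect it the same way in both arms.

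In Data Analysis, exempt the primary outcome from the normality pre-test and name one primary analysis: an overdispersed count model of the treatment-period count on group. Quasi-Poisson is the safer default, with negative binomial if it converges. Use log observed time as offset and baseline bleed count as the main covariate, keep other covariates few given the expected number of bleeds, and report the rate ratio with 95% CI. Analyse the follow-up window the same way as secondary.

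The cost is some protocol wording and a 3-month recalled bleed history at baseline, with the recall error that brings. The change will not rescue power at low bleed rates, and the article should not suggest that it does.

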### Intervention

Patients will continue their factor VIII or factor IX concentrate treatment as prescribed by their referring hematologists. Throughout the study, the prescribed pharmacologic treatment, dosage, and periods of substitute treatment of the participants will not be altered. Participants in the control group will receive no physical therapy using self-myofascial release and will continue with their usual routine of physical activity and exercise. Outcomes will be assessed under the same conditions as those of the experimental group.

At the beginning of the study, the main investigator will explain the characteristics of the intervention to be carried out to the experimental group. Each session will last approximately 15 minutes, with 5 physiotherapy sessions over a period of 3 months. Each patient will perform the interventions at home. Participants will have free access to the mobile app. Access to the platform will be approved after the patient signs the informed consent form. Once the study is complete, the contents of the app (Table 1) will be available on the website of the Hemophilia Physiotherapy research group (InHeFis).

The protocol for self-myofascial release of the lower limbs using a foam roller and solid ball massage, adapted to patients with hemophilic ankle arthropathy, will include self-myofascial release of the plantar, back of the leg, and hamstring regions, as well as adductor, abductor, and pelvitrochanteric muscles. Table 1 shows the physiotherapy protocol. Periodic follow-up will be performed, through phone calls and by SMS text messages, to answer questions from patients regarding the use of the app.

A mobile app (designed by the research group) will be used to demonstrate all the exercises in the self-myofascial release protocol. Each time the patient exercises, he or she will be able to watch a video explaining the characteristics of each exercise (time, repetitions, position, and action). This free app will also collect adherence data recorded as days of exercise by the participant.

Patient will need to have a suitable floor mat. A massage ball will be used for pressure point massage (solid ball massage), typically 40 mm to 50 mm in diameter, made of a hard polyurethane, but slightly padded. Two smooth low-deformability foam rollers (90 cm in length and 15 cm in diameter) will also be used.

**Table 1 table1:** Physiotherapy protocol using self-myofascial release for patients with hemophilic ankle arthropathy.

Region and exercise aid		Action	Observations	Times

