## Methods

### Study Design

This study is designed as a randomized controlled multicenter clinical trial (ClinicalTrials.gov; NCT03914287) to establish the safety and efficacy of a physiotherapy intervention consisting of self-myofascial release using a foam roller. Once eligibility is determined, participants will be randomized to either the intervention (experimental) group or the control group.

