**Achilles region**				
	Foam roller	The movement shall be performed from the most distal part of the leg to the region of myotendinous connection with the calf muscles.	The exercise is to be assisted with slight plantar flexion and extension movements by the patient. The exercise can be enhanced by crossing a leg in extension over the leg subject to the work stimulus	15 slow sliding movements

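### The Intervention section gives 5 sessions over 3 months where the Abstract gives 5 per week: 5 planned sessions against about 60 to 65

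*Protocol article*

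**What the plan says.** The schedule appears twice in the protocol article.

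- Abstract, Methods paragraph: "Each session will last 15 minutes with 5 physiotherapy sessions per week for a period of 3 months".
- Methods, Intervention: "Each session will last approximately 15 minutes, with 5 physiotherapy sessions over a period of 3 months".

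The rest of the Intervention section describes how the treatment is delivered but gives no frequency:

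- On setting: "Each patient will perform the interventions at home".
- On the app's videos, which a patient can watch at each exercise occasion: "he or she will be able to watch a video explaining the characteristics of each exercise (time, repetitions, position, and action".
- On adherence: "This free app will also collect adherence data recorded as days of exercise by the participant".

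The Times column of Table 1 gives seconds, repetitions or movements within a session; the entry for the Achilles region, for instance, is "15 slow sliding movements". The Results and Discussion sections give no session frequency either.

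**The concern.** The number of sessions is a core part of the dose in an exercise trial. The Study Design section gives the purpose as "to establish the safety and efficacy of a physiotherapy intervention consisting of self-myofascial release using a foam roller", and the Abstract names ankle joint bleeding as the primary outcome. Rolling pressure on arthropathic limbs five times in total is a different exposure from doing it five times a week, both for benefit and for bleeding risk.

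The Methods is the operative section, and on its literal wording it prescribes a small fraction of the dose in the Abstract. Because patients exercise at home, no schedule of therapist visits would bring the error to light. Adherence is logged as days of exercise, so its planned denominator would be either 5 or about 60 to 65, depending on which sentence is followed.

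**Working it through.** **Inputs**

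- Session length: 15 minutes (Abstract; 'approximately' in the Intervention section).
- Abstract: 5 sessions per week for 3 months.
- Intervention section: 5 sessions over 3 months.
- Weeks in 3 months: not given. Assumed to be 12 to 13.

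**Formulas**

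- Planned sessions = sessions per week × weeks.
- Total exercise time = sessions × 15 minutes.
- Average spacing under the literal reading = days in the period ÷ 5.

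**Results**

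| | 12 weeks (84 days) | 13 weeks (91 days) |
|---|---|---|
| Abstract: sessions | 5 × 12 = 60 | 5 × 13 = 65 |
| Abstract: total time | 60 × 15 = 900 min = 15.0 h | 65 × 15 = 975 min = 16.25 h |
| Intervention section: sessions | 5 | 5 |
| Intervention section: total time | 5 × 15 = 75 min = 1.25 h | 75 min = 1.25 h |
| Ratio, Abstract to Intervention section | 60/5 = 12 | 65/5 = 13 |
| Intervention section as share of Abstract | 5/60 = 8.3% | 5/65 = 7.7% |
| Average spacing, literal reading | 84/5 = 16.8 days | 91/5 = 18.2 days |

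The Abstract's schedule cannot yield 5 sessions in total at any plausible length for three months, so the difference is not one of rounding.

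**What it does to an adherence figure.** Take a hypothetical patient who logs 10 exercise days, one session a day. Against 5 planned sessions that is 10/5 = 200%. Against 60 to 65 it is 10/60 = 16.7% to 10/65 = 15.4%.

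**Which reading is intended.** Session length, the number 5 and the three-month period agree between the two sentences; only 'per week' differs. Home delivery, a video for each exercise occasion and a log of exercise days all suit a frequent regimen far better than one session every 17 to 18 days. The likely explanation is two dropped words. The documents do not confirm it.

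**The case against.** The strongest reply is that this is a wording slip that the article resolves itself. The full schedule is printed in the Abstract, and the home setting, app and exercise-day log in the Intervention section make five sessions in three months implausible. The 12- to 13-fold gap would arise only if someone delivered the literal reading, and nothing suggests that anyone plans to. The Data Analysis section names no per-protocol set, adherence analysis or dose-response model that would need a planned-session count; it says "We will use the intent-to-treat method to include all individuals who were randomized in the final data analysis". Finally, a journal article condenses a fuller protocol, so sites and patients may never work from this sentence.

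Much of this stands. An attentive reader will probably reach the right schedule, no stated analysis changes, and the point is an internal inconsistency rather than a poor choice of regimen. Three things limit the reply:

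- The contextual clues make the literal reading unlikely, but none of them states a frequency. A reader still has to decide that the Abstract overrides the Methods, when an abstract should summarise them.
- The condensed format excuses what is left out. It does not excuse a count that is stated and contradicts another.
- Whether the app and patient instructions carry the right schedule cannot be seen from the article. That is no evidence of a fault there, but it is reason enough to check.

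**Conclusion.** The concern holds. The Intervention section as written gives 5 sessions (75 minutes in total), while the Abstract implies 60 to 65 sessions (900 to 975 minutes), a 12- to 13-fold difference. The range rests on taking three months as 12 to 13 weeks; the contradiction itself rests on no assumption. That the Abstract is correct and the Methods dropped two words is likely but remains an inference.

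The consequence is limited to the stated dose and the reading of adherence. Sample size, significance level and the intention-to-treat comparison are untouched, and the exercises are otherwise defined. It should be corrected because it misstates the dose of the treatment under test in the section meant to define it.

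**What to change.** Once the sponsor confirms the intended schedule, amend the sentence in the Intervention section to read: 5 physiotherapy sessions per week over a period of 3 months. Before recruitment starts (planned for September 2020), check that the app and the patient instructions state the same schedule, so that logged exercise days are read against about 60 to 65 planned days.

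The cost is a two-word correction and a brief check of existing materials. Design, sample size and analysis do not change.
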